**Background and Rationale**

In Karachi, Pakistan, the incidence of TB is believed to be particularly high, with13,332 patients registered under the National TB Control Programme (NTP) in 2007. Increasingly, the problem of non-compliance is leading to the emergence of multi-drug resistant TB (MDRTB), a form of TB that is more expensive and difficult to treat. Of 7,185 new pulmonary cases studied in Karachi in 2006, 12% were reported to have defaulted on treatment. The system currently recommended by the World Health Organization (WHO) for tackling the problem of non-compliance is Directly Observed Therapy Short-Course (DOTS), which involves on-site, in-person monitoring of compliance with medication. DOTS programmes in Karachi use health workers, health clinic staff, or treatment supporters, who are usually family members, as monitors. However, there is no way of verifying whether and to what extent patients are complying with their drug regimen.

Remote reminders free patients from their dependence on unreliable health workers. IRD is conducting a randomized control trial to gauge the impact of the *Zindagi SMS* system on treatment outcomes for patients with drug-susceptible TB.

**The *Zindagi SMS* System**

The *Zindagi SMS* reminder system is a two-way medication reminder system for people with drug-susceptible tuberculosis. Participants are sent daily medication reminder SMS messages and are asked to respond with an SMS to indicate that they have taken their medication for the day. If the system does not receive a response within two hours, a second reminder is sent. If the system does not receive a response for another two hours, a third and final reminder is sent. Participants who are non-responsive for a week are followed up with a phone call.

Participants are offered PKR 60 per month, as compensation for the cost of sending SMS messages.

**Research Methods**

This study is a randomized control trial that will take place in Karachi, Pakistan. Participants will be recruited through TB clinics throughout the city.

*Participant Inclusion/Exclusion Criteria*

The sample for this study will be drawn from newly diagnosed TB patients with sputum or bacteriologically-positive drug-susceptible TB who are at least 15 years of age in Karachi, Pakistan. Study participants will be required to own a cell phone or have access to one. To reduce spillover effects, patients will be excluded from the study if another household member is already participating. Finally, to enable follow up surveys, participants will have to intend to reside in Karachi throughout their treatment period.

*Recruitment, Randomization, and Data Collection*

When a clinic diagnoses a new patient with tuberculosis, the study’s clinic representative will inform the participant about the study. If a patient meets the eligibility criteria, they will be read an oral informed consent form and will be asked to participate in the study. Emphasis will be placed on explaining that they can refuse to take part in the study without there being any effect on the standard treatment provided to them by the clinic. They will also be informed that participation will require several interviews over the course of the patient’s treatment. Recruitment of minors (below the age of 18) will require the patient's asset as well as informed oral consent from the patient's parent/guardian.

If a participant consents to participate in the study, clinic representatives will then complete a brief enrolment form, including the patient’s name, age, sex, clinic location, as well as other contact information. Random assignment in this study will occur on a rolling basis as new patients are diagnosed with tuberculosis. Patients will be randomized through an electronic randomization process at the time of enrolment, to prevent personal bias from contaminating the randomization process. Patients will be randomized into either the control arm or the *Zindagi SMS* arm of the study using programs on the clinic representatives' mobile phones. Participants will be informed of their randomization status but it will not be shared with their treating clinics by the study representatives.

If the patient is selected into *Zindagi SMS,* the clinical representative will explain the program to the patient, provide him/her with an informational brochure, and provide him/her with a number to call for assistance.

Data collection for the study will occur in three stages for participants in both the *Zindagi SMS* and control groups: Baseline, Midline Surveys, and Endline surveys. The three stages will occur over the standard course of treatment for tuberculosis. The Baseline survey will occur during Month 1 of treatment, Midline data collection will occur on a monthly basis during Month 2 through to Month 7 of treatment (or Month 5 of treatment for participants on the six-month regimen), and the Endline survey will occur after the completion of the expected treatment period. Sputum samples will be attempted from patients after their first, second, fifth and sixth or seventh months of treatment. Each stage of data collection will be voluntary, include informed consent, and be conducted in the patient’s home or in private to ensure confidentiality. All survey questions will be extensively field-tested prior to use in the study in order to be sure that all material covered is culturally sensitive and respectful of local beliefs.

Baseline Survey: Survey enumerators will attempt to visit newly diagnosed TB patients within a week of diagnosis. The baseline survey will collect background information on socio-demographic factors as well as other health conditions.

Midline Surveys: Compliance checks will be attempted every month between Month 2 and Month 7 (or Month 5 for those on an six month regimen) after enrolment. During these months, research staff will conduct unannounced visits to ask participants whether they took their medication in the past 24 hours, and a range on questions about their treatment, health, mobile phone usage, and employment. Urinalysis tests will also be used to objectively gauge compliance.

Endline Survey: After the end of the expected treatment period, enumerators will revisit study participants to conduct a final endline survey. The endline survey will collect information on their health, treatment, as well as attitudes toward compliance with drug regimes.

Clinical outcomes form: Using the patient's District TB number, clinically reported treatment outcomes will be retrieved through the clinic registers. This will enable use clinically reported results to compare outcomes across treatment and control groups.

*Sample Size*

We calculated a minimum sample size of 1,094 per arm to detect an effect size of 5%, from a treatment completion rate of 75% to 80%.

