- Gender : Women in Pakistan often have restrictions on their mobility. Therefore, an SMS reminder system may be more beneficial to them, as they receive reminders in the comfort of their homes. Women are also more likely to be at home, thereby enabling greater access to the owner of the mobile phone (if it is not the patient herself), as they will be home whenever the owner of the mobile phone is at home. Alternatively, women may be less comfortable with technology and therefore there may be less likely to use the system. Moreover, TB stigma is more prevalent in women, especially young women, and so they may benefit from a remote system that sends messages to them at home.
- Vulnerable Populations: We will be looking at the impact of the system on vulnerable populations. In order to look at whether a participant is vulnerable, we will be looking at a variety of variables related to education, gender, and socioeconomic status. Less vulnerable respondents may be more likely to benefit from the intervention, as they may have better health-seeking behaviour and so a reminder system may result in them acting on the reminders. Alternatively, there may be more of an impact on those of a lower socio-economic group, as they may have worse health-seeking behaviour to begin with and, therefore, the system may have a greater impact on them. We will construct a family of indicators that measure socioeconomic status and test for a heterogeneous treatment effect by socioeconomic status.
- Access to a Mobile Phone: We will be looking at the impact of the system based on participants’ relative access to a mobile phones. The extent of access to mobile phones will be determined by ownership of the phone and familiarity with SMS at baseline. We will also look at factors such as literacy of the patient, literacy of their household members, and the language they use to SMS. Increased access to the mobile phone may increase compliance, because the patient will personally be able to see the messages, which could result in improved compliance. Alternatively, patients that have less personal access to the mobile phone may be reminded family members who have greater access, which could increase their compliance, as they will be monitored by the owner of the mobile phone.

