- Quality of Care: We will also be looking at the quality of care received by patients as a sub-group to analyze. Quality of care will be determined by the clinic the patient receives treatment from, whether or not they have a treatment supporter, and whether there is anyone who reminds them to take their medication. We hypothesize that the lower the quality of care, the more impact the system will have, as it will enhance the quality of their care through reminders. However, if the quality of care is so poor that there is a lack of availability of the medication, then this may result in a reduced impact of the system, as it cannot over-ride issues of a lack of availability of medication.
- People likely to respond to Interactive Reminders: We will also use those who are more likely to respond to SMS reminders as a sub-group to analyze. It may be that those who respond more get a greater benefit from the intervention. Thus, we will look at various socio-demographic variables such as gender, age, socio-economic status, literacy, education, and education of other family members, to see whether these are have a significant correlation with response rates for people in the Interactive Reminders arm. Once that is determined, we will examine the impact of Interactive Reminders on this sub-group.

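### The phone-access and quality-of-care subgroups rest on items not listed on the enrolment form that the SMS programme, or knowing one's arm, can change

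*Protocol*

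**What the plan says.** The Protocol, Research Methods (Recruitment, Randomization, and Data Collection), gives this order. After consent, clinic representatives "complete a brief enrolment form, including the patient’s name, age, sex, clinic location, as well as other contact information". Allocation follows on the spot: "Patients will be randomized through an electronic randomization process at the time of enrolment". Next, "Participants will be informed of their randomization status", and for anyone assigned to the SMS arm "the clinical representative will explain the program to the patient, provide him/her with an informational brochure".

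The baseline survey is a separate, voluntary stage with its own consent, held at home or in private. Its window is "The Baseline survey will occur during Month 1 of treatment" and its operational target is "Survey enumerators will attempt to visit newly diagnosed TB patients within a week of diagnosis". Its content is described only as socio-demographic background and other health conditions.

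The section on the Zindagi SMS System describes daily messages that ask for a reply, with up to two further reminders on the same day. It gives no date for the first message and does not make messaging wait for the survey.

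Under Analysis, Sub-group Analysis, phone access is determined by "ownership of the phone and familiarity with SMS at baseline". Quality of care is determined by the clinic, by having a treatment supporter, and by "whether there is anyone who reminds them to take their medication". No time point is given for the quality-of-care items.

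**The concern.** A subgroup comparison keeps the protection of randomisation only if the variable that defines the subgroup cannot be affected by allocation. Here the stage named baseline falls after allocation, after disclosure of the arm and after the SMS arm has had the programme explained.

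Two kinds of item are exposed:

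- **SMS familiarity.** An SMS-arm patient has been shown a two-way texting system and may have been answering it daily.
- **Treatment supporter and reminder person.** Reminding is what the intervention does. A patient in a reminder programme may answer differently, and the household may behave differently.

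If some SMS-arm patients change category and their control counterparts do not, the strata no longer hold exchangeable patients. A difference between strata can then appear or vanish without any real heterogeneity. The quality-of-care hypothesis, that poorer care means more benefit, is particularly exposed, because allocation can move patients out of the group that nobody reminds.

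No later analysis can recover pre-allocation values that were never recorded.

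**Working it through.** **1. Which subgroup items have a listed pre-allocation source?**

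| Subgroup family | Listed on the enrolment form | Not listed there | Can allocation plausibly change it? |
|---|---|---|---|
| Gender | sex | none | no |
| Vulnerable populations | sex | education, socioeconomic status | hardly; only arm-related non-response or reporting |
| Phone access | none | phone ownership, SMS familiarity, literacy, SMS language | yes for SMS familiarity |
| Quality of care | clinic | treatment supporter, anyone who reminds | yes for both |
| Likely responders | sex, age | literacy, education, socioeconomic status | hardly; only non-response or reporting |

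Four of the five families need some item that is not listed. Only two of them use an item that the intervention or knowledge of the arm can readily change.

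**2. The plan's own figure, used only for scale.** The Protocol gives 1,094 per arm for 75% against 80%. The usual two-proportion formula, with two-sided 5% significance and 80% power (both assumed, as neither is stated), gives

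n = [1.960 × √(2 × 0.775 × 0.225) + 0.842 × √(0.75 × 0.25 + 0.80 × 0.20)]² / 0.05² = 1,094.

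The figure reproduces and is not in question.

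**3. Reclassification with no true effect.** All inputs are assumed: 60% of patients truly SMS-familiar, success 80% if familiar and 70% if not, the same in both arms. A share m of unfamiliar SMS-arm patients is recorded as familiar, and these movers have 80% success. Success among those still recorded as unfamiliar in the SMS arm is (0.70 − 0.80m) / (1 − m), against 70% in control.

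| m | Unfamiliar, SMS arm | False effect (points) |
|---|---|---|
| 2% | 0.684/0.98 = 69.8% | −0.2 |
| 5% | 0.660/0.95 = 69.5% | −0.5 |
| 10% | 0.620/0.90 = 68.9% | −1.1 |
| 20% | 0.540/0.80 = 67.5% | −2.5 |
| 40% | 0.380/0.60 = 63.3% | −6.7 |

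If the movers are average unfamiliar patients (70% success), the unfamiliar stratum is unbiased and the familiar one is diluted: (0.48 + 0.28m) / (0.60 + 0.40m). At m = 20% this is 0.536/0.68 = 78.8%, or −1.2 points against 80%. At m = 40% it is 0.592/0.76 = 77.9%, or −2.1 points.

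**4. Effect on the contrast between strata.** A second assumed model has a true effect of 5 points in both strata, half the patients with high access, and control success of 80% (high) and 70% (low). A share m of SMS-arm low-access patients moves up, with control-level success q.

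- High stratum: [0.5 × 0.85 + 0.5m(q + 0.05)] / (0.5 + 0.5m) − 0.80
- Low stratum: (0.70 − mq)/(1 − m) + 0.05 − 0.70

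False interaction (high minus low), in points:

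| m | q = 60% | q = 70% | q = 80% |
|---|---|---|---|
| 2% | −0.6 | −0.2 | +0.2 |
| 5% | −1.5 | −0.5 | +0.5 |
| 10% | −2.9 | −0.9 | +1.1 |
| 20% | −5.8 | −1.7 | +2.5 |

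The sign depends on who moves. The size depends on how many move and how selected they are.

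**5. Scale against sampling error.** An unfamiliar stratum of 0.40 × 1,094 ≈ 438 per arm has a standard error for the difference of √(2 × 0.70 × 0.30 / 438) = 0.031, or 3.1 points. A false −2.5 points is below one such standard error.

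**The case against.** The case on the other side is substantial, and much of it stands.

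- **Not every subgroup is affected.** A reader might infer that the intervention can alter membership of all of them. The documents do not support that. Sex, age and clinic are on the enrolment form, and reminders can hardly change education, literacy or socioeconomic status within a month. For those items the remaining risk is that a voluntary, unblinded visit is completed or answered differently by arm.
- **The enrolment list may be incomplete.** It is introduced as what the form includes, and eligibility already requires owning or having access to a phone. It would be too strong to say that the other items are certainly collected later. However, the form is described as brief, socio-demographic background is assigned to the survey, and SMS familiarity is tied to baseline, which is the Protocol's name for the later stage.
- **The two timing statements do not conflict.** A visit within a week of diagnosis lies inside Month 1. It is still only an attempt, and it still follows allocation and disclosure.
- **Messages before the visit are not established.** The first-message date is not given, so earlier SMS exposure is a possibility read from silence. Disclosure and the programme explanation, by contrast, are placed at enrolment, and these alone can affect answers.
- **The plan does not firmly predict that phone owners will start reminding.** Family monitoring is offered as one of two competing hypotheses.
- **No covariate adjustment is proposed.** A warning about adjusting for these variables would criticise an analysis that the Protocol does not contain.
- **Reclassification of 20% to 40% is a demanding assumption.** Questionnaires that are not shown might also ask about the time before diagnosis. The size is therefore uncertain, though the gap in the Protocol's text remains.

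**Conclusion.** The point holds for two prespecified secondary analyses: phone access, through SMS familiarity, and quality of care, through treatment supporter and reminder person. As written, the Protocol allows these items to be collected after allocation and disclosure, so the subgroups can differ in make-up between arms.

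The size cannot be derived from the Protocol. In the no-effect illustration, the false effect among unfamiliar patients is about 1 point or less when 10% or fewer move, and 2.5 to 6.7 points when 20% to 40% move selectively. The contrast between strata can go either way. In the second illustration it runs from −5.8 to +2.5 points, and reaches −2.9 points at 10% only if the movers are poor-prognosis patients. All of these figures rest on assumed prevalences, success rates and reclassification shares.

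A reader might set the larger figures beside the 5-point design effect and infer a threat to the main result. There is none: the primary comparison is by intention to treat on clinic-recorded outcomes and uses no survey variable, and the sample size is unaffected. This is a cheap improvement, not a correction on which the trial depends.

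**What to change.** Add four items to the electronic enrolment form: phone ownership, SMS familiarity, treatment supporter, and whether anyone already reminds the patient. Lock the form before the phone program releases the allocation. State in the Analysis section that the survey-type items of the phone-access and quality-of-care subgroups are defined from those locked values only, alongside the clinic recorded at enrolment.

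If an item has to stay in the home survey, word it to refer to the time before enrolment, and report survey timing and completion by arm. The same report covers the remaining non-response risk for education, literacy and socioeconomic status, so those items need not move.

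The cost is a few more minutes at enrolment and an edit to the phone form, with no extra patients, staff or visits. The change helps only patients enrolled after it is made.

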**Analysis**

Analysis of this study will be conducted using intention to treat. Participants randomized to the *Zindagi* SMS group will be considered a part of that group for analysis, regardless of whether they used the SMS system or not.

*Primary Outcome*

The primary outcome for this study is clinically-recorded treatment outcomes. Treatment outcomes for TB patients include cure, treatment complete, treatment failure, died, transfer out, or default. These are reported by TB clinics to the National TB Control Program on all their patients on treatment. We will look at treatment success rates of patients in our study, as recorded by their TB clinics, to compare the means for these outcomes between our intervention and control groups.

*Secondary Outcomes*

There are a number of secondary outcomes for this study:

Medication adherence: Medication adherence will be measured through urinalysis tests and self-reports by participants on whether they took their medication in the past 24 hours. This data will be collected during unannounced midline visits.

Phyical fitness and mobility: Physical fitness will be measured through questionnaires conducted with participants during household visits each month that they are on treatment. The physical fitness index will look at the self-reported ability of respondents to complete certain tasks.

Pyschological impacts: In order to cause of the psychological impacts of the system, the investigators will look at participants’ perceptions of the likelihood of being cured, how healthy they feel on a given day, and how supported they feel.

Sputum conversion: Sputum samples will be collected and we will look at the difference in when sputum conversion occurs between the *Zindagi SMS* and control groups.

*Sub-group Analysis*

In order to test the differential effects of the intervention on various sub-groups, we will be conducting the following sub-group analysis.

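### The arm is concealed from the treating clinics but not, as far as stated, from home-visit staff or urine readers, and the monthly visit that measures adherence also asks about phone usage

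*Protocol*

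**What the plan says.** **Concealment.** Under Research Methods (Recruitment, Randomization, and Data Collection), participants learn their allocation at enrolment, and study representatives do not pass it to the treating clinics. No other group is named as kept unaware of the arm.

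**The midline visit.** The same section says that "research staff will conduct unannounced visits to ask participants whether they took their medication in the past 24 hours", together with "a range on questions about their treatment, health, mobile phone usage, and employment". It then adds: "Urinalysis tests will also be used to objectively gauge compliance". Visits run monthly from Month 2 to Month 7, or to Month 5 on the six-month regimen. Both arms are surveyed.

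**Outcomes from these visits.** Under Analysis (Secondary Outcomes): "Medication adherence will be measured through urinalysis tests and self-reports by participants on whether they took their medication in the past 24 hours", and "This data will be collected during unannounced midline visits". For fitness: "Physical fitness will be measured through questionnaires conducted with participants during household visits each month that they are on treatment". The psychological outcome covers "participants’ perceptions of the likelihood of being cured, how healthy they feel on a given day, and how supported they feel", with no visit named.

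**The intervention.** The Zindagi SMS System section describes one to three messages a day, a requested reply, a monthly payment towards SMS costs, and a phone call after a week without response.

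**Primary outcome.** This is the treatment outcome recorded by the TB clinic and retrieved from clinic registers.

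**The concern.** The intervention runs on the participant's phone. A visit that asks an unmasked participant about phone use invites mention of the study messages, the replies or the payment. The interviewer who hears this may be the one recording whether today's dose was taken, or asking for urine. Once the arm is known or guessed, prompting, the coding of unclear answers and persistence in getting a specimen can differ between arms without anyone intending it.

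Urinalysis is the protocol's objective check on self-report. An assay can be objective while the decision to press for a sample, or the reading of a borderline result, is not. If both adherence measures are exposed to the same influence, the second cannot be relied on to correct the first. An apparent adherence or fitness benefit could then partly reflect how the data were collected.

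**Working it through.** **Step 1. Who is stated to know the arm**

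| Party | What the protocol states |
|---|---|
| Participant | Knows the arm from enrolment |
| Treating clinic | Not told by study representatives |
| Home-visit research staff | Nothing stated |
| Reader of the urine test | Nothing stated; the reader is not identified |

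Concealment was considered and applied to one group. The clinics report the primary outcome. The home-visit staff record much of the secondary data and are not covered.

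**Step 2. Which outcomes are exposed**

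| Outcome | Collected at the monthly visit? | Exposure |
|---|---|---|
| 24-hour self-report | Yes, stated | Interviewer and participant |
| Urine adherence | Yes, stated | Collection; reading if unmasked |
| Self-rated fitness | Monthly household visits, stated | Interviewer and participant |
| Psychological items | Visit not stated | Cannot be placed |
| Sputum conversion | Collector and visit not stated | Cannot be placed |
| Clinic-recorded treatment outcome | No, from registers | None by this route |

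**Step 3. How often it arises.** Months 2 to 7 give 6 visits and Months 2 to 5 give 4. At the minimum sample of 2 × 1,094 = 2,188 participants, that is 4 × 2,188 = 8,752 to 6 × 2,188 = 13,128 scheduled visits.

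**Step 4. Are monthly phone data needed?** The Sub-group Analysis section defines phone access by ownership and SMS familiarity at baseline. The subgroup of likely responders rests on replies to reminders, which the system itself receives. No named analysis requires phone-usage items every month.

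**Step 5. Sensitivity of the comparison (illustration only).** The sample size is reproduced first, because it sets n. The assumptions are two-sided 5%, 80% power and 1:1 allocation, none of which the protocol gives:

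n = [1.960·√(2·0.775·0.225) + 0.8416·√(0.75·0.25 + 0.80·0.20)]² / 0.05² = (1.1575 + 0.4961)² / 0.0025 ≈ 1,094 per arm. This matches the stated figure.

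Now suppose adherence is truly equal in the two arms, but recording raises one arm from p to p + b. The probability of a significant result favouring that arm is

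Φ{ [b√n − 1.960·√(2p̄(1−p̄))] / √(p(1−p) + (p+b)(1−p−b)) }, where p̄ = p + b/2.

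For p = 0.75, b = 0.02: [0.6615 − 1.1838] / 0.6038 = −0.865, and Φ = 0.19.

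| Artefact b | p = 75% | p = 85% |
|---|---|---|
| 1 point | 8% | 10% |
| 2 points | 19% | 27% |
| 3 points | 38% | 54% |

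With no artefact the figure would be 2.5% in that direction. The base rates and b are assumptions, and the calculation takes one binary result per participant with nobody missing. It shows that a trial of this size would react to a small artefact. It does not show that an artefact of any given size will occur.

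**The case against.** The strongest reply is that much of the mechanism is not in the text. Several tempting readings go further than the protocol does:

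- **That the interviewer will certainly learn the arm.** Phone questions go to both arms, all participants own or have access to a phone, and the wording of the items is not given. Disclosure is plausible, not established.
- **That urine is taken after the phone questions.** The midline paragraph lists topics; it is not a questionnaire sequence. If its order did count, 24-hour adherence, treatment and health would all come before phone usage.
- **That one person interviews, collects the urine, reads it and obtains sputum.** The protocol does not say so, nor that the same staff member returns each month.
- **That the phone items prime the ratings of support.** No visit or position is given for the psychological items.
- **That the urine measure is unprotected.** The accurate statement is that no protection is described. A test result is less open to influence than self-report, and unannounced visits limit preparation by the participant.
- **That the bias rivals the 5-point effect in the sample size.** That effect concerns treatment completion, a register-based outcome that these visits do not touch.

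It can also be said that item order and specimen handling belong in a field manual, and that participants who know their arm would colour their self-reports whatever the staff knew. Both points have weight, but neither disposes of the concern. Who is kept unaware of the arm is a design matter that the protocol itself takes up and settles for clinics only. Participant awareness cannot be removed; staff awareness can be reduced.

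**Conclusion.** The concern holds in a limited form. The protocol describes no masking of home-visit staff or urine readers, and it puts potentially arm-revealing questions into the visit that yields self-reported and urine adherence. Self-rated fitness, asked at monthly household visits, shares the exposure. These secondary outcomes are open to interviewer and collection bias by arm.

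The primary outcome is unaffected by this route. The size and direction of any bias cannot be derived from the document, and the illustrative probabilities rest wholly on assumed values. The conclusion also assumes that no masking rule exists in field procedures not shown here. If one does, the protocol need only state it. The point should be acted on because the protection is nearly free and the adherence findings would be hard to defend without it.

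**What to change.** 1. **Extend the concealment.** State in Research Methods that the arm is also withheld from home-visit staff. Issue visit lists without the arm. Where staffing allows, do not assign staff who make the one-week non-response calls to visit those same participants.
2. **Re-order or move the phone items.** At the midline visit, ask them last, after the adherence and fitness items are recorded and urine is collected. Alternatively, drop them from the monthly form and ask them at endline only. Do not simply shift them to baseline: that survey follows randomisation and disclosure, so open questions on current phone use could reveal the arm before the first midline visit. Limit any baseline items to phone ownership and SMS familiarity before enrolment, which is what the phone-access subgroup mainly uses.
3. **Mask the urine reading.** Read and record results by study ID without the arm shown.
4. **State what remains.** Report self-reported adherence and fitness as coming from participants who know their arm.

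**Cost.** One questionnaire re-ordered, the arm removed from field lists, and some constraint on staffing. Phone-usage data become less frequent if the items move to endline. Some participants will still disclose their arm, so the change reduces the bias without removing it.
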